## Methods

### Design

We chose a type 2 hybrid effectiveness-implementation design to evaluate the effectiveness of the clinical interventions and the implementation strategies.^20–23^ Mixed methods will be used as the method of evaluation. DR care pathway was developed by the Kerala Health Secretary, non-communicable diseases lead, Health and Medical Education service providers, technical and EHR teams, local authorities and the GCRF/UKRI-funded coapplicants from the UK. The DR care pathway will be set-up in a staggered approach with five FHCs initiated in the first 3 months and the remaining 11 centres will be added based on acceptance of all stakeholders and adapting and training phase for 12 months from 15 March 2018. A further 12–15 months will be allocated to recruit consenting patients to a cross-sectional study to gather quantitative data for the effectiveness outcomes. A minimal data set from this study will also be entered into EHR to enable future screening for the consented patients. Qualitative data collection from interviews of staff, patients and focus groups at baseline and end of study and all field notes gathered during the study will be utilised to inform evaluation of the implementation strategy.^20–22^

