### Description of the standard of care

Currently, patients with diabetes are not systematically screened for DR in the public health system. Most patients present to the tertiary centre voluntarily either because of increased awareness of complications of diabetes or due to visual impairment. Therefore, the current standard of care will be captured as the number of patients presenting to the tertiary centre for an eye consultation for DR over a period of time as there is no baseline data in the primary and secondary care. This cross-sectional survey of the patients presenting at the FHCs will provide information on the uptake of screening of people registered in the non-communicable diseases register at the start of the study. The prevalence of DR and STDR of the screened population will be estimated from the numbers screened in all the non-communicable diseases registers during this period.

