	Recruit, designate and train for leadership	A project manager will be recruited to manage the programme under the supervision of the non-communicable diseases lead. The Health Secretary will conduct periodic meetings with the project team to assess performance.
	Obtain formal commitments	A collaborative agreement is in place between Government of Kerala and Moorfields Eye Hospital, London, UK outlining their roles and responsibilities in the implementation of the DR care pathway.
	Prepare patients to be active participants	Community level health workers will prepare patients to be active in their care, to ask questions and specifically to inquire about care guidelines, the evidence behind clinical decisions or about available evidence-supported treatments. Each patient will provide written consent to be screened for DR in this project as well as participate in interviews after verbal consent.
	Inform local opinion leaders	The Health Minister of the Kerala state and members of the local government will be briefed on the project and encouraged to be champions of the project to enable scale up to all family health centres in the state.
Finance	Access new funding	Use GCRF/UKRI funding to purchase smartphone retinal cameras and retinal lasers, develop EHR, train staff at family health centres and secondary care, employ project manager, data entry operators and personnel to conduct interviews, create study database linked to hand-held applications for data entry operators. State and local government funds will be sourced for scale up.
	Incentivisation	ASHAs will be incentivised to accompany participants with diabetes who are referred to secondary care for treatment.
Education	Develop educational materials	Develop DR training modules and retinal image capture modules for family health centres staff Develop laser training material to train ophthalmologists.
	Distribute educational materials	Distribute educational materials (including guidelines, manuals and toolkits) in person, by mail and/or electronically. Multiple training sessions are planned at each family health centres. The camera manufacturers will be invited to provide hands-on training on capturing good quality retinal images. Training on laser surgery will also be provided to the ophthalmologists at secondary care.

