### Data collection

#### Quantitative data

Effectiveness outcomes will originate from the data sources shown in table 2. Data collected by nurses or data operators from the EHR include age, gender, duration of diabetes, use of insulin, parental history of diabetes, other complications of diabetes including diabetic kidney disease, cardiovascular complications, and diabetic foot, random blood sugar results, urine dipstick test for albuminuria and blood pressure record. Other study-specific data collected by nurses or data operators on the day of screening include education status, occupation and income categories, and previous history of DR, cataract surgery or any other ocular history. In addition, they will measure body mass index, waist circumference and complete a lifestyle questionnaire on smoking, diet, physical activity, EQ-5D vision bolt-on.^24^ The EQ-5D vision bolt-on will be used to calculate the quality adjusted life-years and utility value for economic analysis. EQ-5D alone does not capture visual acuity deficits.^25^ The EQ-5D vision bolt-on asks patients to rate their health across six dimensions: mobility, self-care, usual activities, pain/discomfort, anxiety/depression and vision. Each dimension is scored in five levels: no problems, slight problems, moderate problems, severe problems and extreme problems. A recent study provided utility values based on EQ-5D vision bolt-on. The mapping was done in a clinical trial cohort with macular oedema in central retinal vein occlusion.^26^

In the reading centre, the data collection will include the grade of retinopathy in both eyes, presence of cataract and gradability of the retinal images. Data collected on referred patients will include numbers with ungradable images due to cataract, treatment options offered for DR and review appointment.

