### Statistical analyses

We will create a complete case data set of the cross-sectional survey for use in the analyses of effectiveness and assess the potential impact of missing data using sensitivity analysis incorporating a range of optimistic and pessimistic scenarios for the impact of missing data. We will model two outcomes that we hypothesised would be influenced by the intervention: (1) uptake of DR screening (primary outcome) and (2) numbers of patients referred for STDR as a result of screening. We will use bivariate logistic regression models to assess crude associations between sociodemographic factors such as age, gender, education, income and living arrangements, and other clinical data with DR and STDR and use fractional polynomials to account for the form of continuous covariates to predict uptake of DR screening. Factors associated with a p<0.25 will be candidates for inclusion in the multivariable logistic regression models. We will test interactions among identified main effects to capture improvement in model prediction assessed by reduced residual variance-based statistics. To account for the staggered entry into the study, we will add a variable indicating the month of entry of each FHCs into the programme (eg, 1. if the FHC join in the first month of the programme, 2. if in the second month and so on). A non-significant coefficient for this variable will suggest the staggered approach had no effect and a significant coefficient will allow the effect to be quantified for each FHC. In our final adjusted model, we will consider associations with a p<0.05 as statistically significant. Adequacy of model discrimination and calibration will be assessed using receiver operating characteristic curves. The validation of the telemedicine will be reported as the agreement (kappa statistics) between screen positive patients graded by the graders at the reading centre versus the DR grade as recorded by the ophthalmologists in secondary care centres. A kappa coefficient of 0.6 or higher was prespecified to indicate validity.

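### The patient-level model of screening uptake is tied to a survey data set that holds essentially no unscreened people

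*Protocol article*

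**What the plan says.** The Statistical analyses section of the protocol article names the data set: "We will create a complete case data set of the cross-sectional survey for use in the analyses of effectiveness". It lists uptake of DR screening, labelled the primary outcome, as the first of two outcomes to be modelled, and says the team will "use fractional polynomials to account for the form of continuous covariates to predict uptake of DR screening". The same paragraph adds a covariate for the month in which each FHC joined and plans ROC curves to judge the models.

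Other sections say who is in the survey:

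- Design: the study will "recruit consenting patients to a cross-sectional study to gather quantitative data for the effectiveness outcomes".
- Description of the standard of care: "This cross-sectional survey of the patients presenting at the FHCs will provide information on the uptake of screening".
- Table 1, in the row on preparing patients to take an active part: "Each patient will provide written consent to be screened for DR in this project".
- Ethics and dissemination: every participant consents in writing before entering the study.

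The section on quantitative data collection takes age, gender, diabetes duration, insulin use and similar items from the electronic health record (EHR). By contrast, "Other study-specific data collected by nurses or data operators on the day of screening include education status, occupation and income categories". In the sample size section, registered people who do not attend appear only within a count: the number on each FHC's register when the survey starts, which is the denominator of the primary proportion.

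**The concern.** A model that predicts whether someone was screened needs records of people who were not. The data set named for the effectiveness analyses is made up of people who came and agreed to be screened. The document therefore names a data set, an outcome and a model that do not fit together.

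At stake is the study's ability to say which registered patients the pathway does not reach. The results are meant to inform state-wide adoption, so that is a useful question. If the plan is followed as written, the analysts will find no usable contrast and will have to choose another one after seeing the data.

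**Working it through.** **1. The plan's own figure.** The sample size section gives 377 × 3 = 1131. With 16 FHCs the mean cluster is 1131/16 = 70.7. A design effect of 3 = 1 + (70.7 − 1) × ICC gives ICC = 2/69.7 = 0.029, which matches the stated value of about 0.03. The article states no proportion, precision or confidence level for the 377. Assuming 0.5, ±5 percentage points and 95%, n0 = 1.95996² × 0.25/0.05² = 384.1. With N = 40 000, n = 384.1/(1 + 383.1/40 000) = 380.5, so 381, which is 1.1% above 377. Nothing below depends on these figures.

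**2. The two sets of people, side by side.**

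| | Survey data set | Baseline register |
|---|---|---|
| Who | Present at an FHC and consent to screening | Everyone registered at survey start |
| Role in the article | Effectiveness analyses, including the uptake model | Denominator of the primary proportion |
| Form | Individual records with covariates | A count per FHC |
| Unscreened people | Essentially none | All of them |

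**3. What the logistic model does with screened records only.** If y = 1 for every record, the log-likelihood is the sum of log(μ), with μ = 1/(1 + exp(−xb)). The score for the intercept is the sum of (1 − μ), which is positive for every finite b. The likelihood therefore keeps rising as the intercept grows, and no finite maximum exists. A ROC curve compares events with non-events. The number of such pairs is n × 0 = 0, so the area under the curve is undefined.

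**4. Numerical illustration.** A register of 40 000 was simulated with slopes of −0.03 per year of age and 0.30 per education level. These values are assumptions, not figures from the article.

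| Simulated uptake | Full register: age slope / education slope | Screened records | Intercept at iterations 5, 10, 15, 20 (screened only) |
|---|---|---|---|
| 5.1% | −0.033 / 0.241 | 2049 | 6.2, 11.2, 16.2, 21.2 |
| 20.8% | −0.030 / 0.309 | 8318 | 6.2, 11.2, 16.2, 21.2 |
| 50.5% | −0.030 / 0.303 | 20 185 | 6.2, 11.2, 16.2, 21.2 |

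On screened records the slopes stay at 0 while the intercept climbs by 1 per iteration. This shows the algebra of step 3 at work. It is not evidence of what the study's data will contain, which rests on the sections compared in step 2.

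**5. If a few non-events exist.** Some people may present and consent but not be screened. Table 2, under equity, plans to report the number denied screening although willing. A model could then run, but it would compare screened attenders with unscreened attenders. It would say nothing about registered people who never came.

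**6. What can still be estimated.** For FHC j, let s be the number screened and N the number on its baseline register. The proportion s/N needs only counts. So does logit(p) = a + b × month of entry, fitted as a binomial regression to 16 pairs (s, N). The DR and sight-threatening DR models use screened people by design and are not touched.

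**The case against.** The best reply is that the article already names wider sources for uptake. Table 2 takes the proportion screened from monthly EHR and study database entries. Table 3 uses the EHR and study database for adoption, and the register and EHR for penetration. Data monitoring refers to anonymised EHR extracts, and Target population says that everyone on the register at survey start will be taken into account. An article also condenses, and the definition of analysis rows is often left to a fuller document.

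This shows that the fix is practical. It does not remove the problem, because none of those statements gives individual register rows to the uptake model, and Statistical analyses assigns the effectiveness analyses to the survey. That is a stated choice, not an omitted detail. The planned optimistic and pessimistic scenarios do not help either: they deal with missing data, whereas a non-attender's uptake is known and it is the record that is absent.

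Several stronger readings are tempting, but the document does not support them:

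- **That education and income are stated predictors of uptake, so that the complete-case rule would remove every unscreened person even after linkage.** The article ties "sociodemographic factors such as age, gender, education, income and living arrangements, and other clinical data" to DR and STDR. The uptake clause mentions only continuous covariates, and several of these come from the EHR. The rule would remove non-attenders only if day-of-screening variables entered the uptake model.
- **That no coefficient can be estimated for uptake.** The month-of-entry effect can be, from FHC counts.
- **That the share of the register missing from the model can be found by subtracting 1131 from 40 000.** The 1131 is a sample size requirement, not a forecast of attendance, and the article does not say that the 40 000 are the people on the 16 registers.

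**Conclusion.** The point holds for one analysis. As written, the patient-level logistic model of uptake, with its ROC assessment, is to be fitted to a data set with no non-events or almost none, and it cannot be meaningfully estimated there.

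A reader might infer that the primary outcome itself fails. It does not: the proportion screened per FHC remains estimable, as step 6 shows.

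The conclusion rests on reading Design, Description of the standard of care, Table 1, Ethics and dissemination and Statistical analyses together, since no single sentence says that the survey holds only screened people. It does not depend on the sample size, the register size or the uptake achieved.

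**What to change.** State that the uptake model uses the same denominator as the primary proportion: one row per person with diabetes on the baseline register of the 16 FHCs, with screened yes or no as the outcome, taken as an anonymised register or EHR extract. Restrict its covariates to those held for screened and unscreened people alike, such as age, gender, diabetes duration, insulin use where recorded, FHC and month of entry. Treat FHC as the clustering unit rather than a set of fixed effects, because month of entry is constant within a centre. State also that variables recorded on the day of screening are used only in models among screened people.

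If individual register rows cannot be extracted, restrict the uptake model to FHC-level binomial regression on screened and registered counts, with allowance for variation between centres.

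The cost is a change of wording and one extra anonymised extract. Education, income and other day-of-screening variables could not be studied as predictors of uptake, but the planned data could not support that anyway. The FHC-level fallback has only 16 units and gives no patient-level predictors.

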### Sample size

We have chosen the proportion of patients in the non-communicable diseases register with diabetes screened for DR as our primary outcome variable.

Justification of the choice of primary outcome: this variable captures the effectiveness of our intervention as well as the fidelity of implementation. Other facts that informed our choice of the primary outcome is that we expect a short implementation time of 7–9 months during which other outcomes such as number of patients treated may not be a feasible option. Therefore, we have estimated the sample size based on this primary outcome.

Our calculations are complicated by the expected increase in number of people with diabetes in the non-communicable diseases register as public awareness of diabetes and DR increases so the denominator of numbers screened will be the number of people registered in the non-communicable diseases in each FHCs at the start of the cross-sectional study. There is no data on the baseline proportion of patients that attend the tertiary centre for screening. The prevalence of diabetes is between 10% and 16% in Thiruvananthapuram of which 8% are estimated to have DR and 3% to have STDR but about 20% may have to be referred. Assuming a finite population of 40 000 patients with diabetes, a simple random sample of 377 patients will be needed. However, we expect large design effects due to clustering patients within FHCs. There is not enough data to calculate the value of this design effect and therefore we assume it to be 3 to give a final sample size of 1131, which is equivalent to assuming a within-FHCs intracluster correlation coefficient of approximately 0.03 (n=16 FHCs) with negligible residual clustering by the intermediate cluster level of ASHAs, where mean cluster size is smaller.

As described by Becker *et al* in mammography screening,^28^ we expect sources of bias in the implementation programme that will likely influence the sample size calculation. Unscreened DR cases that already exist in the community may contribute to an over-estimation of the effect of screening. We expect lead-time bias because of our short implementation period and so some DR in the community may be missed. A comparison of numbers with DR in FHCs with longer implementation period with those of shorter period may adjust for this bias. We intend to provide a descriptive analysis as well as a temporal comparison using time series analysis.

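### The month-of-entry test ignores the FHC clustering that the sample size allows for: at the plan's own design effect, its nominal 5% level is really about 26%

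*Protocol article*

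**What the plan says.** The Sample size section of the protocol article takes clustering seriously. It states: "However, we expect large design effects due to clustering patients within FHCs". Having no data from which to estimate the design effect, it says "therefore we assume it to be 3 to give a final sample size of 1131", and adds that this is "equivalent to assuming a within-FHCs intracluster correlation coefficient of approximately 0.03 (n=16 FHCs". It also considers a second level of clustering, by community health worker, and treats it as negligible.

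The Statistical analyses section then describes the modelling in some detail. It begins: "We will use bivariate logistic regression models to assess crude associations between sociodemographic factors". Factors below p<0.25 "will be candidates for inclusion in the multivariable logistic regression models". Fractional polynomials, interactions, a p<0.05 rule in the final model and ROC curves follow. For the staggered start, "we will add a variable indicating the month of entry of each FHCs into the programme". The section also fixes how to read that term: non-significance is taken to mean that staggering made no difference, and significance is taken as grounds to quantify the effect for each FHC.

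The section names no random effect, GEE, cluster-robust variance or survey-design adjustment. The Discussion mentions robust statistical techniques, but in connection with design limitations, selection bias and confounding, not clustering.

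**The concern.** The two sections do not fit together. One says that patients in the same FHC resemble each other enough to triple the sample. The other brings the FHC into the model only through its month of entry. That is a fixed covariate: it can absorb a trend over entry months but not the rest of the variation between centres.

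The term most exposed is month of entry itself. Every patient in a centre shares its value, so extra patients add little information about it. A model that counts patients as independent gives it too small a standard error, and the plan attaches a yes/no conclusion to its p-value. The likely harm is a reported effect of staggering, with effects quantified for each FHC, that is only ordinary variation between centres. The Discussion itself expects centres to differ in facilities, socioeconomic mix and staff.

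**Working it through.** **Inputs from the protocol article, Sample size:** population 40 000, simple random sample 377, design effect (DEFF) 3, final size 1131, ICC about 0.03, 16 FHCs. **From Statistical analyses:** significance at p<0.05. **Assumed, because not stated:** two-sided tests, and for the 377 an anticipated proportion of 0.5, a margin of ±5 points and 95% confidence.

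**1. The plan's own figures.** The plan says: "Assuming a finite population of 40 000 patients with diabetes, a simple random sample of 377 patients will be needed".
- n0 = 1.96² × 0.5 × 0.5 / 0.05² = 384.1
- With the finite population correction, 384.1 / (1 + 383.1/40 000) = 380.5, close to 377. The small difference plays no part here.
- 377 × 3 = 1131, as stated.
- Mean cluster size m = 1131/16 = 70.7
- DEFF = 1 + (m − 1) × ICC, so ICC = 2/69.7 = 0.0287, which agrees with about 0.03. (ICC 0.03 gives DEFF 1 + 69.7 × 0.03 = 3.09.)

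**2. A covariate constant within FHCs (month of entry).** The correct standard error is √DEFF = √3 = 1.73 times the ordinary one.
- Real type I error = 2 × (1 − Φ(1.96/√3)) = 0.258
- Real coverage of a nominal 95% interval = 1 − 0.258 = 0.742
- With DEFF 3.09 the type I error is 0.265.

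**3. A patient-level covariate with its own intracluster correlation ρx.** DEFF = 1 + (m − 1) × ICC × ρx = 1 + 2ρx. The ρx values are assumptions.

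| ρx | DEFF | Real level of a nominal 5% test |
|---|---|---|
| 0 | 1.0 | 5.0% |
| 0.05 | 1.1 | 6.2% |
| 0.10 | 1.2 | 7.4% |
| 0.20 | 1.4 | 9.8% |

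**4. Check by simulation.** Ordinary logistic regression was fitted to beta-binomial data with no true effects: 16 FHCs of 71 patients, ICC 0.0287, mean uptake 0.5, and an illustrative entry pattern with five centres in the first 3 months. In 4,000 runs the rejection rates were 25.8% for month of entry, 4.7% for a patient covariate with ρx = 0, and 7.1% for one with ρx = 0.10. With mean uptake 0.2 (3,000 runs) they were 23.9%, 4.9% and 5.8%. In a separate simulation at ICC 0.03, regressing the 16 FHC proportions on month of entry rejected 5.4% to 5.9% of the time, so the same data support a valid test.

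**5. Larger clusters.** If the model used the whole register, taken as 40 000/16 = 2,500 per FHC with the ICC unchanged, DEFF = 1 + 2,499 × 0.0287 = 72.7 and the real level for month of entry would be about 82%. Both the size and the ICC are assumptions at that scale.

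**The case against.** The best defence is that this is a condensed article. It never says that patients are independent, a mixed or GEE model is still logistic regression, and a statistical analysis plan that is not shown may specify the variance. That stands as far as it goes: a reader might infer that the team dropped clustering altogether, and the article does not establish that. But the article does more than stay silent. It fixes how the FHC enters the model and attaches a decision rule to that term, and the rule as written gives the wrong error rate.

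Three stronger readings are tempting and are not supported.

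- **Every p-value in the models is invalid.** The factors the plan lists, such as age, gender, education and income, are patient-level, and step 3 shows only mild inflation for them at about 71 per FHC.
- **The interval for the primary uptake proportion is far too narrow.** The article gives no interval method for it. Table 2 reports uptake for each FHC, and variation between FHCs does not enter a centre's own proportion. Between-FHC variance matters only for an overall figure meant to generalise beyond these 16 centres. As an illustration at 50% uptake and n = 1131, the half-width is 1.96 × √(0.25/1131) = 2.9 points without clustering and 1.96 × √(3 × 0.25/1131) = 5.0 points with it.
- **The real level is 82%.** The plan does say that "the denominator of numbers screened will be the number of people registered in the non-communicable diseases in each FHCs", counted when the survey begins. However, the analysis is on a complete-case survey data set, and Data collection says that education, occupation and income are recorded on the day of screening. Models with those factors could not cover the unscreened register.

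Nor does the article tie scale-up to these p-values. Table 3 bases the district plans on clinical and cost-effectiveness data.

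**Conclusion.** The concern holds for the month-of-entry rule and should be fixed. On the plan's own design effect, the nominal 5% test has a real type I error of about 26%, and the matching 95% interval covers about 74%. This rests on three things: that the models are fitted as ordinary logistic regression, as the text reads; that the assumed design effect is about right (the article says there are too few data to estimate it); and that about 71 patients per FHC are analysed. With more patients per FHC at the same ICC the error would be larger, but the article does not settle how many would be modelled.

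For patient-level covariates the problem is minor, at about 5% to 10% over the assumed range. The point estimate of uptake is not affected.

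**What to change.** In Statistical analyses, add that:

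- all logistic models include a random intercept for FHC, or use GEE clustered on FHC with a small-sample correction suited to 16 clusters;
- month of entry is tested against between-FHC variation, for example by regressing the 16 FHC-level proportions on month (16 − 2 = 14 residual degrees of freedom), and its coefficient is reported with an interval on the same basis;
- any interval for overall uptake that is meant to apply beyond these 16 FHCs allows for clustering.

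If an analysis plan already says this, a cross-reference is enough. It would also help to reword the rule for month of entry so that non-significance is not read as no effect, because a test based on 16 centres will have limited power.

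The cost is a few lines of text and wider intervals. No new data and no change in sample size are needed, because the 1131 already includes the design effect.

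### The month-of-entry coefficient cannot show that staggering had no effect when non-significant, nor give an effect for each FHC when significant

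*Protocol article*

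**What the plan says.** Under Statistical analyses, to allow for the staggered start, the plan states that "we will add a variable indicating the month of entry of each FHCs into the programme", coded 1, 2 and so on. Two readings follow in one sentence: "A non-significant coefficient for this variable will suggest the staggered approach had no effect and a significant coefficient will allow the effect to be quantified". The second of them, given in full, is that "a significant coefficient will allow the effect to be quantified for each FHC". The threshold in the final adjusted model is that "we will consider associations with a p<0.05 as statistically significant". The article gives no power, equivalence range or interval criterion for this coefficient.

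Under Design, five FHCs start in the first three months and "the remaining 11 centres will be added based on acceptance of all stakeholders", with an adapting and training phase. No selection rule is given for the first five. Table 1 and the Abstract treat the joining of further centres as evidence that the pathway is acceptable and feasible.

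Under Sample size, the plan expects strong clustering: a design effect of 3, equated with an intracluster correlation of about 0.03 across 16 FHCs. On lead-time bias, the same section says: "A comparison of numbers with DR in FHCs with longer implementation period with those of shorter period may adjust for this bias".

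**The concern.** Including the variable as an adjustment is reasonable. The problem is the interpretation attached to it.

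- **Non-significant result.** A p-value above 0.05 is compatible with no effect and with any other value inside the confidence interval. With 16 distinct units that interval is wide however many patients are screened.
- **Significant result.** One numeric covariate yields one slope, shared by every FHC. It carries no information on how staggering acted in a particular centre.
- **Meaning of the slope.** If centres that were readier to take part joined sooner, and readier centres also screen more of their register, the slope mixes the timing of entry with readiness.

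The study could therefore report that staging made no difference, or attach effects to named centres, when its data support neither statement.

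A smaller related issue is the lead-time comparison under Sample size. It is framed on numbers with DR, which depend on how many people each FHC has screened.

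**Working it through.** **The plan's own figures.** 377 × 3 = 1131, as stated. 1131/16 = 70.7 patients per FHC. ICC = (3 − 1)/(70.7 − 1) = 0.0287, which agrees with the stated value of about 0.03. The base of 377 is close to what a 95% interval of ±5 points at 50% gives for a population of 40 000 (381); the difference of 4 does not bear on this point.

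**Inputs from the article.** 16 FHCs; ICC 0.03; significance level 0.05, taken as two-sided; five FHCs entering in months 1–3.

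**Assumed inputs.**
- The 11 later FHCs enter over months 4–12, so first and last entry are 11 months apart. The SD of entry months is 3.56, so Sxx = 15 × 3.56² = 190.1.
- Uptake is near 50%, so p(1 − p) = 0.25.
- Patients per FHC (m) are 71 (1131/16) or 2,500 (40 000/16). The second value supposes that the 40 000 is the combined register of these 16 FHCs, which the article does not say.
- The analysis allows for clustering. I approximated it by a regression of 16 FHC proportions on month, with 16 − 2 = 14 df.

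**Formulas.**
- Variance of an FHC proportion: V = 0.25 × [ICC + (1 − ICC)/m].
- Standard error of the slope: SE = √(V/Sxx).
- 95% half-width, first to last entry: 2.145 × SE × 11.
- Difference detectable with 80% power: (2.145 + 0.868) × SE × 11.
- Power for a given difference: noncentral t with 14 df.

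**Results at ICC 0.03.**

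| | m = 71 | m = 2,500 |
|---|---|---|
| V | 0.25 × (0.03 + 0.97/71) = 0.01092 | 0.25 × (0.03 + 0.97/2,500) = 0.00760 |
| SE (points per month) | 0.758 | 0.632 |
| 95% half-width | 17.9 points | 14.9 points |
| Detectable, 80% power | 25.1 points | 21.0 points |
| Power, true 10 points | 20% | 27% |
| Power, true 15 points | 39% | 52% |

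Moving from 71 to 2,500 patients per FHC changes little, because the number of FHCs sets the limit. For example, an observed 10-point difference would be non-significant, with an interval of about −8 to 28 points (m = 71) or −5 to 25 points (m = 2,500). The rule would read either result as suggesting no effect.

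**Sensitivity.** At ICC 0.01 the detectable difference is 18.6 points (m = 71) or 12.3 points (m = 2,500); at ICC 0.10 it is 40.3 or 38.1. The most favourable of these cases, ICC 0.01 with 2,500 per FHC, still has only 63% power for 10 points. In a closely similar calculation at ICC 0.03 and 70.7 per FHC, shortening the entry period to 9 months moved the detectable difference only from 24.3 to 23.5 points.

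**Effect for each FHC.** Write the linear predictor for FHC j as a + b × month_j + other terms. The part due to entry is b × (month_j − 1), so two FHCs that join in the same month receive the same value by construction. Giving each FHC its own effect would need FHC indicators, and month_j is an exact linear combination of those. A separate staggering effect per centre is therefore not identifiable. This step needs no numerical assumption.

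**Readiness.** As an illustration, simulated data had no staggering effect, ICC 0.03, 71 patients per FHC, and all between-FHC variation due to readiness. With a readiness-to-entry-order correlation of 0.3, 0.5 or 0.7, a valid cluster-level test was significant in about 16%, 33% or 63% of runs. The spurious first-to-last differences were about 7, 12 and 17 points. The simulation let readiness order all 16 FHCs, whereas the article states acceptance only for 11, so it shows the mechanism and is not an estimate.

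**The case against.** The strongest reply has several parts.

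- **The wording is hedged and the variable is only an adjustment.** The text says a result will suggest something, and the Discussion concedes that causal inference is difficult without a concurrent control. This softens the rule but leaves its direction wrong, and the caveat is not applied to this coefficient.
- **The phrase about each FHC may be loose.** It could mean the slope multiplied by each centre's entry month. That is a legitimate fitted value, but it is not an effect of staggering estimated in that centre, and the text does not make the distinction.
- **The magnitude rests on assumptions.** This stands. The entry schedule, 50% uptake and 2,500 per FHC are not in the article. A reader might infer that a 10–15 point difference would usually be reported as no effect. That holds for 10 points, but for 15 points only at 71 per FHC; at 2,500 per FHC such a difference would be detected slightly more often than not (52%).
- **The article does not say how clustering enters the model.** That may be left to an analysis plan, so it cannot be inferred that clustering is ignored. If it were, the error would run the other way: at a design effect of 3, a nominal 5% test would be falsely significant about 26% of the time.
- **Acceptance governs only part of the roll-out.** A reader might infer that all 16 FHCs joined in order of acceptance. Design says this of the later 11 only, and stakeholder acceptance might even mean agreement at programme level. Confounding by readiness is plausible but not established.
- **The lead-time comparison is tentative.** The text says it may adjust, and Description of the standard of care already plans prevalence among those screened. Design also places cross-sectional recruitment after the staggered phase, so counts need not simply rise with time open. It would be too strong to say that the comparison adjusts for nothing.

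**Conclusion.** The concern holds for the interpretation rule under Statistical analyses. Non-significance on 16 points cannot suggest that staggering had no effect: with clustering allowed for and the stated assumptions, the interval is about ±15 to ±18 points. A true 10-point difference would be missed about 73–80% of the time, and a 15-point difference about 48–61%. The exact figures move with the ICC and the entry schedule; the fault in the reasoning does not. That one slope cannot yield FHC-specific effects follows from the coding alone. That the slope may include readiness is a reasonable caution for the 11 later FHCs.

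A reader might infer that the state-wide scale-up decision hangs on this coefficient. The documents do not support that: Table 3 bases the scale-up plan on clinical and cost-effectiveness data, and staging is judged by the addition of centres, monthly reports and interviews. The primary proportion screened is not affected. What changes is what the study may conclude about staggering. The lead-time comparison is a secondary matter of choosing the right measure.

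**What to change.** Under Statistical analyses, delete both readings. Replace them with a statement that the month-of-entry slope will be reported with its 95% confidence interval, from a model that allows for clustering by FHC with about 14 df. Describe it as an association that may include FHC readiness. Show uptake by FHC separately, not derived from the slope.

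Under Sample size, make the comparison of longer- and shorter-running FHCs on the proportion with DR among those screened, in line with Description of the standard of care, instead of on numbers with DR.

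The cost is a few sentences and no new data. The downside is a more modest claim about staggering.
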